### 5.2.3 Subject Withdrawal Criteria and Procedures

#### **5.2.3.1 Enrollment Time Point**

A subject is considered eligible for the study after signing an informed consent form approved by the ethics committee, meeting all inclusion criteria, and not meeting any exclusion criteria. The official enrollment time point is defined as the moment the EDN catheter is introduced into the subject’s body.

#### **5.2.3.2 Withdrawal**

Although withdrawal without cause is discouraged, subjects may withdraw from the clinical trial at any time, with or without explanation, and this will not affect their future medical care.

The investigator may also discontinue or withdraw a subject from the study for the following reasons:

Occurrence of an unanticipated adverse device effect (UADE) that poses significant or unreasonable risk to the subject.

- Any condition arising during the trial that could harm the subject (e.g., pregnancy, inability to continue follow-up assessments, hypersensitivity to the study device or contrast medium).

Inability of the subject to complete the required study procedures or follow-up.

- All subjects enrolled in the trial (including those who withdraw or are lost to follow-up) will be documented. Withdrawn subjects will not be replaced, and no additional follow-up will be conducted. Investigators should document the reason for withdrawal whenever possible.
- If withdrawal is related to the safety or efficacy of the study device or procedure, the investigator should seek subject consent to continue clinical monitoring outside the trial. Data collected prior to withdrawal will be retained and included in analyses, but no further data will be collected after withdrawal.

#### **5.2.3.3 Enrollment Control**

The study will enroll at least 30 subjects, with no restrictions on the number of subjects recruited at each participating center.

## 5.3 Evaluation Methods

### 5.3.1 Primary Endpoints

#### **5.3.1.1 Primary Safety Endpoint**

The primary safety endpoint is the incidence of composite major adverse events (MAE)* related to the investigational device and/or ablation procedure occurring intraoperatively or within 30 days post-baseline procedure.

- MAE is defined to include the following events:
- Hypoglycemia or hyperglycemia requiring hospitalization.
- Vascular complications requiring surgical repair, interventional treatment, thrombin injection, or blood transfusion.
- Celiac/hepatic artery dissection or perforation requiring intervention.
- Significant embolic events leading to end-organ damage or requiring intervention to prevent end-organ damage.
- Acute liver injury or liver failure.
- All-cause mortality.

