| **Endpoints** | **Primary Endpoints:**   - The occurrence of composite major adverse events (MAE) related to the device and/or the procedure within 30 days post-procedure. MAE includes the following events:  1. Hypoglycemic or hyperglycemic events requiring hospitalization 2. Vascular complications requiring surgical repair, interventional treatment, thrombin injection, or blood transfusion 3. Celiac/hepatic artery dissection or perforation requiring intervention 4. Significant embolic events leading to end-organ damage or requiring intervention to prevent end-organ damage 5. Acute liver dysfunction or liver failure 6. All-cause mortality  - The change in glycated hemoglobin (HbA1c) at 6 months post-procedure compared to baseline levels.   **Secondary endpoints:**   - The changes of Hba1c from baseline at 1, 3, 12 and 24 months post procedure - The changes of assessment of β-cell function and insulin resistance (Homeostatic Model Assessment for β-cell function and insulin resistance, HOMA-β/HOMA-IR) - The changes of mean glucose, postprandial glucose increase, nocturnal glucose increase and time in range (TIR, 3.9-10.3 mmol/L) by 14 - day continuous glucose monitoring (CGM) - The changes of blood lipids (triglycerides, total cholesterol, high- and low-density lipoprotein) - The changes of liver function (alanine aminotransferase, aspartate aminotransferase, alkaline phosphatase and gamma - glutamyl transferase) - The changes of renal function (urea nitrogen, blood creatinine and eGFR) - The changes of glucose, insulin and C - peptide in oral glucose tolerance test (OGTT) - Proportion of patients achieving target HbA1c (< 7.0% and ≤6.5%) - Proportion of patients with HbA1c < 7% without hypoglycemia/severe hypoglycemia or weight gain - Proportion of patients with the changes of in type/dose of antidiabetic drugs - Incidence of hypoglycemia and severe hypoglycemia (blood glucose level < 3.9 mmol/L) - The occurrence of new significant celiac or hepatic artery stenosis at 6 months post procedure (stenosis >50% as assessed by CT angiography and confirmed by digital subtrationsubtraction angiography when CT angiography assessment shows abnormal) - The occurrence of device and/or procedure-related adverse events and serious adverse events - Incidence of cardiovascular and cerebrovascular complications (defined as cardiovascular death, myocardial infarction and ischemic stroke) - Quality of life assessment (EQ-5D-5L) |

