| **Statistical Methods** | **Sample size estimation:**  No formal sample size calculation was performed. However, the sample size of 30 (treated) was determined based on the hypothesis that patients would experience a reduction in HbA1c at 6 months. To achieve a predefined 1.0% reduction in HbA1c, with a standard deviation of 1.5%, a sample size of 26 would be required to yield a lower two-sided 95% confidence bound of approximately 0. Taking into account a 10% drop out rate, the estimated sample size is 29.  **Populations for analysis:**  Baseline characteristics were analyzed in all enrolled patients. The treated patients were analyzed for safety profile, and patients with follow-ups were analyzed for efficacy.  **Analysis of primary endpoints:**  All adverse events were recorded by and assessed by all investigators for the association with the device or procedure. HbA1c reductions at 6 months were measured for patients with 6-month follow-up and expressed as mean with a 2-sided 95% CI.  The success criterion for this study is defined as no device- or procedure-related MAE occured and achievement of HbA1c reduction at 6 months. |

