# 6. Statistical Considerations

## 6.1 Primary Endpoints

Primary Safety Endpoint

Incidence of composite major adverse events (MAE)* related to the investigational device and/or ablation procedure occurring intraoperatively or within 30 days after the baseline procedure.

* MAE includes:

- Hypoglycemia or hyperglycemia requiring hospitalization.
- Vascular complications requiring surgical repair, interventional therapy, thrombin injection, or blood transfusion.
- Celiac/hepatic artery dissection or perforation requiring intervention.
- Significant embolic events causing end-organ damage or requiring intervention to prevent end-organ damage.
- Acute liver injury or liver failure.
- All-cause mortality.

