## 12.3 Causality Assessment with Investigational Device/Procedure

Investigators shall assess relatedness of each reported event to the investigational device and to the study procedure (per MDCG 2020-10/1, Table 12-2), and assess relatedness to antiplatelet therapy (Table 12-3).

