**Table 12-2. Criteria for Assessing Relationship Between Investigational Device/Procedure and AE**

| **Relatedness** | **Definition** |
| --- | --- |
| **Not related** | The event can be excluded as related when one or more of the following apply: no temporal relationship with device use or procedure; reaction pattern inconsistent with known device effects and biologically implausible; stopping/decreasing or re-using/increasing exposure has no effect (when clinically feasible); involves a body part not affected by device/procedure; explained by other causes (baseline disease/comorbidity, another device/medication/therapy, other risk factors); if applicable, unrelated to an erroneous diagnostic result from the device. (Not all conditions are required; depends on device/procedure and event type.) |
| **Possibly related** | Weak association to device/comparator use or procedure cannot be excluded; may be attributable to other factors (baseline disease/comorbidity and/or another device/medication/therapy). When relatedness cannot be assessed or information is pending, classify as possibly related. |
| **Probably related** | Event appears related to device use or procedure and/or cannot be reasonably explained by another cause. |
| **Causally related** | Relationship is beyond reasonable doubt when (as applicable): known side effect of this product class or similar devices/procedures; temporal relationship present; involves body part affected by or influenced by the device/procedure; follows known reaction pattern; de-challenge/re-challenge affects the event (when feasible); alternative causes adequately excluded; injury due to use error; if applicable, caused by erroneous diagnostic result from the device. (Not all items are required; depends on device/procedure and event type.) |

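### The primary safety composite lists death from any cause but counts only device- or procedure-related events, so read literally a 30-day death judged unrelated is not counted.

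*Protocol*

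**What the plan says.** The primary safety endpoint is stated four times in the protocol: in the opening Clinical Study Protocol Synopsis (Endpoints), in the second Protocol Synopsis (Primary Endpoints), in section 5.3.1.1 and in section 6.1. Each time the relatedness condition is attached to the composite as a whole:

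- Opening synopsis: "The occurrence of composite major adverse events (MAE) related to the device and/or the procedure within 30 days post-procedure".
- Section 5.3.1.1: "The primary safety endpoint is the incidence of composite major adverse events (MAE)* related to the investigational device and/or ablation procedure".
- Section 6.1: "related to the investigational device and/or ablation procedure occurring intraoperatively or within 30 days after the baseline procedure".

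The second synopsis is worded in the same way. Each statement then lists six components, the last of which is death from any cause ("All-cause mortality" in section 5.3.1.1). None exempts death from the relatedness condition.

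The decision rule appears only in the opening synopsis, under Statistical Methods: "The success criterion for this study is defined as no device- or procedure-related MAE occured and achievement of HbA1c reduction at 6 months".

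Relatedness is for the investigators to decide. The opening synopsis says "All adverse events were recorded by and assessed by all investigators for the association with the device or procedure", and section 12.3 says "Investigators shall assess relatedness of each reported event to the investigational device and to the study procedure". Section 12.2 treats death as the outcome of a specific SAE rather than as an event in itself.

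**The concern.** Under a relatedness filter the label all-cause has no effect, because the component becomes related death. The endpoint then has two readings. In one, the filter governs and an unrelated death is dropped. In the other, the specific label governs and every death counts. They differ in exactly the case where it matters, a death within 30 days that the investigators attribute to something else.

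Two features of the design give this weight. The safety part of the success criterion tolerates no events, so a single classification decides it. The trial also has no control arm, so nothing within it shows how many deaths to expect without the procedure. A report could describe a composite that includes all-cause death and show a rate of zero although a patient had died.

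**Working it through.** The protocol gives no expected MAE rate, performance goal or safety sample size, so there is no safety figure to reproduce. The check compares the texts and then works through one scenario.

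**Which endpoints would catch the death?** Take a non-cardiovascular death within 30 days, judged not related.

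| Endpoint | Condition | Counted? |
| --- | --- | --- |
| Primary MAE composite (5.3.1.1, 6.1, both synopses) | related to device and/or procedure | not if read literally |
| Success criterion, safety part (opening synopsis) | related MAE | not if read literally |
| AEs and SAEs (5.3.2) | related to device and/or procedure | no |
| 3MACE (5.3.2) | cardiovascular death, myocardial infarction or ischaemic stroke, at 12 and 24 months | no |

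Such a death would be reported as a safety event under section 12.2, but no other endpoint in section 5.3.2 is defined to count it.

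**Effect on the rate.** Inputs: n = 30 (section 6.3); no related MAE; one unrelated death within 30 days. Intervals are exact (Clopper-Pearson) 95%.

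- Filter applied to death, x = 0: rate 0/30 = 0%. Upper limit 1 − 0.025^(1/30) = 0.1157. Interval 0 to 11.6%. The safety half of the success criterion is met.
- Death counted whatever its cause, x = 1: rate 1/30 = 3.3%. Lower limit 1 − 0.975^(1/30) = 0.0008. The upper limit solves (1 − p)^30 + 30p(1 − p)^29 = 0.025, giving p = 0.172. Interval 0.1 to 17.2%. The safety half fails.

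The opening synopsis also mentions 37 patients. With that number the results are 0/37 (0 to 9.5%) and 1/37 = 2.7% (0.1 to 14.2%), and the verdict reverses in the same way.

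**How likely is the scenario?** The protocol gives no 30-day death risk, so the risks here are assumptions. The chance of at least one death among 30 patients is 1 − (1 − q)^30:

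| Assumed 30-day risk q of an unrelated death | Chance of at least one in 30 |
| --- | --- |
| 0.05% | 1.5% |
| 0.1% | 3.0% |
| 0.5% | 14.0% |
| 1% | 26.0% |

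The exclusion criteria (recent major cardiovascular events, severe complications, life expectancy under 12 months) make the lower rows more plausible.

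**The case against.** The best defence is that the specific term controls. Section 5.3.1.1 defines MAE by a list, the list names death from any cause, and a sensible reader would count every death. That reading is possible, so one cannot say that the protocol expressly excludes an unrelated death. But no sentence says that death is exempt, and the success criterion, which repeats the relatedness condition without exception, points the other way. Two tenable readings of a primary endpoint with opposite verdicts are a defect in themselves.

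It is also fair to say that the stakes are limited. Sections 6.2 and 6.4 plan no formal hypothesis test, the success criterion appears only in the opening synopsis, the scenario is improbable, and the two intervals overlap widely. The difference bites only through the zero-event rule.

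A reader might infer more than the protocol supports:

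- *All six components should count whatever their attribution.* The other five carry no all-cause label, so restricting them to related events is coherent. Without a control arm, attribution is the only means of separating procedural harm from background events. Under a zero-event rule, one background glycaemic admission would otherwise fail the trial. Such a redesign is debatable and is not needed to remove the contradiction.
- *The protocol fails to say which causality grades count as related.* That mapping is commonly left to the SAP, which is not at hand. Table 12-2 is also cautious on doubtful cases: "When relatedness cannot be assessed or information is pending, classify as possibly related".
- *The sponsor decides attribution.* Section 20.2 has the sponsor and CRO safety team classify events by the adverse event definitions. It does not give them the relatedness decision, which section 12.3 assigns to investigators.
- *The death would go unreported.* It would not. Section 12.2 requires all AEs and SAEs to be reported, and the trial report must cover the adverse events observed.
- *The trial would be declared a success.* Only the safety half would be met. An HbA1c reduction at 6 months is also required.

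**Conclusion.** The point holds. All four statements of the primary safety endpoint contradict themselves on death, and the success criterion carries the restriction forward. One death within 30 days judged unrelated moves the reported MAE result from 0/30 (0 to 11.6%) to 1/30 = 3.3% (0.1 to 17.2%), and moves the safety half of the success criterion from met to failed, depending only on which reading is taken. If the death is non-cardiovascular, no other listed endpoint records it.

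This rests on n = 30, on no other MAE occurring, and on reading the relatedness condition as governing the whole list, as its position and the success criterion suggest. It does not rest on any assumption that investigators would misattribute events. The contradiction concerns death alone.

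**What to change.** In the opening synopsis, the second synopsis, section 5.3.1.1 and section 6.1, define the primary safety endpoint as the incidence, intraoperatively or within 30 days after the procedure, of either (a) death from any cause, or (b) any of the other five listed components when related to the device and/or procedure. In the opening synopsis, change the safety part of the success criterion to: no death from any cause and no other device- or procedure-related MAE within 30 days. The HbA1c part stays as it is.

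The cost is wording in these places and, under section 11.2, ethics committee approval of the amendment. No new data are needed, because section 12.2 already requires all AEs and SAEs to be reported whatever their cause. The downside is that an unrelated death would make the MAE rate and the success verdict less favourable. Showing the attribution of each death beside the composite lets readers weigh that.

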# Protocol Synopsis

| **Endovascular Denervation for the Treatment of Type 2 Diabetes** | |
| --- | --- |
| **Objective** | To evaluate the safety and efficacy of the Endovascular Denervation System (including generator and catheter) manufactured by Shanghai Golden Leaf Med Tech (Brattea) Co., Ltd., when performing endovascular denervation (EDN) in the celiac trunk and hepatic artery for the treatment of type 2 diabetes mellitus (T2DM). |
| **Device** | Endovascular Denervation Generator and Catheter |
| **Control Device** | None |
| **Device Specifications** | - Endovascular Denervation Catheter  \| **Model** \| **Specification** \| **Number of Electrodes** \| **Stent Type** \| **Length (mm)** \| **Maximum Expansion Diameter (mm)** \| \| --- \| --- \| --- \| --- \| --- \| --- \| \| GL-6W \| 08 \| 6 \| Net \| 1150±10% \| 8 \| \| 12 \| 6 \| Net \| 1150±10% \| 12 \|  - Endovascular Denervation Generator: Model: GL-06E (6×15 W, temperature-controlled, 12.1-inch LCD resistive touchscreen display) |
| **Study Design** | Prospective, multicenter, single-arm feasibility clinical trial |
| **Study Population** | Patients with poorly controlled T2DM, defined as those who, despite treatment with metformin in combination with one to three oral antidiabetic drugs (OADs) and/or insulin, still fail to achieve adequate glycemic control, with HbA1c levels between 7.5% and 10.5%. |
| **Planned Sample Size** | 30 |
| **Planned Participating Hospitals** | Zhongda Hospital, Southeast University  The First Affiliated Hospital of University of Science and Technology of China (Anhui Provincial Hospital)  Shandong Provincial Hospital |
| **Primary Endpoints** | Primary Safety Endpoint: Incidence of composite major adverse events (MAEs) related to the investigational device and/or ablation procedure occurring intraoperatively or within 30 days post-procedure.  MAEs include:   - Hypoglycemia or hyperglycemia events requiring hospitalization - Vascular complications requiring surgical repair, interventional therapy, thrombin injection, or blood transfusion - Celiac/hepatic artery dissection or perforation requiring intervention - Significant embolic events resulting in, or requiring intervention to prevent, end-organ damage - Acute liver injury or hepatic failure - All-cause death   Primary Efficacy Endpoint: Change in HbA1c from baseline to 6 months post-procedure. |

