**Antiplatelet Therapy**

To minimize thrombotic complications, antiplatelet therapy (monotherapy) should be initiated before the procedure, such as aspirin (ASA) or a P2Y12 inhibitor (clopidogrel preferred; ticlopidine may be used if intolerant). Subjects already receiving ≥72 hours of ASA or a P2Y12 inhibitor do not require a loading dose.

Otherwise, a loading dose must be given before or no later than 2 hours after the baseline procedure.

**Recommended minimum loading doses:** ASA 300 mg, clopidogrel 300 mg.

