# 9. Risk–Benefit Analysis

## 9.1 Risks and Adverse Events Related to Endovascular Procedures

Risks are similar to those for patients undergoing comparable vascular interventions outside the study and may include, but are not limited to:

- Allergic reactions (to contrast agents, devices, medications, etc.)
- Access-site complications (bleeding, hematoma, AV fistula, pseudoaneurysm, infection, pain)
- Thrombosis/thrombus formation
- Embolization (air, tissue, thrombus, or material-related)
- Renal impairment or failure
- Pyrexia
- Infection/sepsis
- Vasospasm or occlusion
- Vascular injury (dissection, perforation, rupture, hemorrhage)
- Retroperitoneal hemorrhage
- Vascular complications requiring surgery
- Transient hemodynamic instability (hypotension/hypertensive episodes)
- Arrhythmias
- Cardiopulmonary arrest
- Death

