## 9.2 Potential Risks Related to the Investigational Device and EDN

- Potential device/procedure-related risks include:
- Pain
- Celiac/hepatic arterial thrombosis or embolization and resultant end-organ injury
- Celiac/hepatic arterial dissection, perforation, rupture, or bleeding
- Vascular injury or aneurysm formation of the celiac/hepatic arteries
- Vasospasm or acute closure of the celiac/hepatic arteries
- Post-EDN stenosis at ablation sites in the celiac/hepatic arteries
- Hepatic dysfunction
- Gastrointestinal adverse reactions (nausea, vomiting, bloating, diarrhea, etc.)
- Orthostatic hypotension
- Post-procedure hypoglycemia
- Skin burns
- Other unforeseeable risks may also exist.

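### The MAE composite counts end-organ damage only when the event is called embolic, so a narrow class of in-situ thrombosis with organ damage falls outside the primary safety endpoint

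*Protocol*

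**What the plan says.** The MAE composite is stated four times, and each time the organ-damage component is confined to embolic events:

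- Section 5.3.1.1: "Significant embolic events leading to end-organ damage or requiring intervention to prevent end-organ damage". The Endpoints row of the Clinical Study Protocol Synopsis uses the same terms.
- Section 6.1: "Significant embolic events causing end-organ damage or requiring intervention to prevent end-organ damage".
- Protocol Synopsis, Primary Endpoints: "Significant embolic events resulting in, or requiring intervention to prevent, end-organ damage".

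The component that could otherwise pick up a thrombosed artery depends on how the event is treated: "Vascular complications requiring surgical repair, interventional treatment, thrombin injection, or blood transfusion" (Section 5.3.1.1). The other four components are glycemic events leading to hospital admission, dissection or perforation needing intervention, acute liver injury or failure, and death.

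Elsewhere the protocol treats thrombosis as a harm in its own right. Section 9.1 has the separate entry "Thrombosis/thrombus formation", distinct from its entry for embolization. Section 9.2 names, as a risk of the device and procedure, "Celiac/hepatic arterial thrombosis or embolization and resultant end-organ injury". The antiplatelet paragraph of Section 5.4.7.6 gives its purpose in the same terms: "To minimize thrombotic complications, antiplatelet therapy (monotherapy) should be initiated before the procedure".

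The Statistical Methods row of the Clinical Study Protocol Synopsis defines study success as no related MAE together with a reduction in HbA1c at 6 months.

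**The concern.** The investigational treatment heats the wall of the celiac and hepatic arteries. A thrombus forming at the ablation site is therefore a local harm that the sponsor foresaw and listed. The primary safety endpoint takes up only the embolic half of that listed risk. For some events, whether organ damage counts then depends on the mechanism written on the form and not on what happened to the patient.

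The success criterion tolerates no MAE at all. In a trial of about 30 treated patients, a single decision between thrombotic and embolic can settle its safety half.

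**Working it through.** **Step 1: run one scenario through the composite.** Take a related thrombus that forms in place in the celiac or common hepatic artery within 30 days, damages the spleen, stomach or pancreas, spares the liver, is not fatal and is managed without surgery or an interventional procedure. Against the six components of Section 5.3.1.1:

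1. Glycemic event leading to hospital admission: not met.
2. Vascular complication needing one of the listed treatments: not met, because none is used.
3. Dissection or perforation needing intervention: not met.
4. Embolic event with organ damage: not met on the wording, because nothing has embolized.
5. Acute liver injury or failure: not met.
6. Death: not met.

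Result: 0 of 6, so not an MAE. Change only the label in item 4 to embolic and the same damage is an MAE, because the first limb of that component needs no intervention.

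**Step 2: see how much of thrombosis is affected.** Change one feature of the scenario at a time:

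- Surgical or interventional treatment is needed: counts under component 2.
- The liver is injured, by whatever mechanism: counts under component 5.
- The patient dies: counts under component 6.

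Only events with all of these features absent, and with damage to another organ, are left out.

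**Step 3: see where the omitted event goes.** It would be recorded as a related adverse event or serious adverse event, whose incidence is a secondary endpoint (Section 5.3.2). It would not enter the success criterion.

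**Step 4: what one event is worth.** The protocol states no MAE rate or limit, so there is no figure of its own to reproduce. Input: n = 30 (Section 6.3). Exact (Clopper-Pearson) two-sided 95% limits:

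- 0 of 30: rate 0%; upper limit 1 − 0.025^(1/30) = 11.6%.
- 1 of 30: rate 1/30 = 3.3%; limits from the beta quantiles, lower Beta(0.025; 1, 30) = 0.1% and upper Beta(0.975; 2, 29) = 17.2%.

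The safety half of the success criterion goes from met to not met.

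**Step 5: how likely such an event is.** The documents give no frequency, so the risk p per patient is an assumption. The chance of at least one event in 30 is 1 − (1 − p)^30:

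- p = 1%: 26.0%
- p = 2%: 45.5%
- p = 3%: 59.9%
- p = 5%: 78.5%

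These values show only how the chance depends on p; none is an estimate for this device.

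**The case against.** **A risk list is not an endpoint definition.** Section 9.2 also lists pain, skin burns, stenosis and "Vasospasm or acute closure of the celiac/hepatic arteries", and a composite is entitled to select. This stands, so a reader should not infer a contradiction between Section 9.2 and the endpoint. The point is narrower: the composite already selects organ damage from a vascular event, then splits by mechanism what Section 9.2 presents as one risk, and gives no reason.

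**Most serious thrombosis already counts.** True, as Step 2 shows. A reader might infer that thrombosis of the treated arteries is left out of the primary endpoint altogether. The text does not support that.

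**The event is not lost.** Also true. It remains a related adverse event, and if serious it goes to the sponsor within 24 hours (Table 12-4). But the secondary endpoint does not feed the success criterion.

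**The wording may be applied broadly.** Section 5.3.1.1 introduces the list with wording that could be read as open-ended. Section 20.2 has the sponsor and CRO safety team classify events under a Safety Plan that is not shown and might hold working definitions. Nothing in the protocol says that embolic covers thrombosis in place, and Section 9.1 separates the two. An open-ended list would leave the primary composite undefined.

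**No bias is shown.** This stands. One might infer that the MAE rate is biased downward. The documents show only that one kind of event could be left uncounted, with no evidence of how often it occurs. The cited study of 11 patients treated in the celiac artery reported no related serious events or major complications (Section 3.2). With 0 of 11, however, the exact two-sided 95% upper limit is 1 − 0.025^(1/11) = 28.5%, so it settles little either way.

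**The trial is descriptive.** Sections 6.2 and 6.4 state no formal hypothesis, and the success criterion appears only in the opening synopsis. That limits the consequence but does not remove it, since the criterion is stated and turns on a zero count.

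**Conclusion.** The point holds in a limited form. All four statements of the composite omit a related, non-fatal thrombosis in place that damages an organ other than the liver and needs no surgical or interventional treatment. The same damage from an embolus counts. The finding rests on reading the component literally and the six-item list as complete; no passage of the protocol says otherwise.

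The gap is small and its frequency unknown. Its weight comes from the zero-MAE success criterion: one such event in 30 is the difference between 0% (upper limit 11.6%) and 3.3% (upper limit 17.2%), and between meeting and failing that criterion. It is worth correcting because the remedy is short and makes the component depend on harm and not on a mechanism label. It does not show that the safety endpoint is invalid or that its result would be wrong.

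**What to change.** In the Endpoints row of the Clinical Study Protocol Synopsis, the Primary Endpoints row of the Protocol Synopsis, Section 5.3.1.1 and Section 6.1, replace 'significant embolic events' with 'significant thrombotic or embolic events'. Leave the rest of each component as it stands, and make the same change on the MAE form.

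Do not add a limit to the celiac and hepatic arteries or their branches. The present wording counts a related embolus in any territory. The procedure runs through a femoral sheath and an aortic catheter (Section 5.5.2.2), and Section 9.1 lists embolization without tying it to the treated arteries. Such a limit would drop emboli elsewhere that cause organ damage without needing intervention, although they count today.

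The cost is two added words in four places and an update to the form. The MAE rate may be slightly less favourable.
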